### Study Procedures

In addition to the standard admission and discharge questionnaires, and standard treatment described below, the 100 consecutive admissions for this study were asked to follow additional data collection procedures and were reimbursed accordingly. In addition to admission and discharge questionnaires, patients were asked to complete 6-month and 12-month follow-up self-report questionnaires. Patients were also asked to visit a laboratory facility at 3-month and 6-month follow-up to obtain a blood draw for a lipid panel (total cholesterol, HDL, LDL, triglycerides) and HbA_1c_. Participants received a US $25 Amazon gift card after completion of each of their admission and discharge assessments, and a US $100 Amazon gift card after the 6-month and 12-month follow-up intervals, for a possible total of US $250 in gift cards for completing all assessments.

### Ethics Approval

This study was approved by Salus Institutional Review Board in January 2019 (approval number: ERC-001) and procedures followed were in accordance with the ethical standards of the institutional review board on human experimentation and the Helsinki Declaration of 1975.

### Treatment

The BETR program is designed to specifically serve the needs of patients struggling with BESD. A case report suggested that having patients with BESD participate in treatment programs designed primarily for restrictive eating disorders may be problematic due to differing foci of weight restoration versus normalizing eating patterns, as well as patients’ comparisons to other patients, which can be detrimental to recovery [24,25]. Although there is little empirical evidence to support this, a study of intensive treatment specifically for patients reporting episodes of overeating (patients with BN, BED, or obesity without binge eating) found improvements in eating disorder psychopathology after 5 weeks, suggesting that targeted specialty care may be more effective and more efficient than general eating disorder treatment programs that address a wide range of symptomatology [26]. In addition, patients with BESD have unique medical concerns that may best be treated in their own programming. For example, compared to healthy controls, patients with BED have been found to be 13 times more likely to develop type 2 diabetes [27]. They are also more likely to exhibit several other medical complications including insulin resistance, hypertension, acid reflux, and obstructive sleep apnea [4,28-30].

Patients receive personalized treatment from a multidisciplinary team for biweekly individual therapy, biweekly psychiatry visits, weekly family therapy, and weekly dietary sessions. Additionally, patients meet with a primary care physician, certified exercise physiologist, case manager, behavioral health counselors, and nurses upon admission and as needed. The registered dietitian and physician jointly decide on meal plans based on patients’ treatment goals and medical conditions. Patients participate in 3 supported meals and 2-3 supported snacks daily. Treatment is focused on regulating eating and treating body image disturbance. The exercise philosophy is on increasing joyful and intuitive movement, increasing mobility when needed, decreasing body shame, and decreasing overexercise or compulsive exercise when present.

In addition to interrupting eating disordered behavior, treatment also focuses on managing comorbid conditions, such as mood and anxiety disorders, and regulating sleep. Patients participate in daily group therapy based on a range of treatment modalities, including enhanced CBT (CBT-E) [16], DBT [17], ACT [18], narrative therapy, and exposure and response prevention, and on a range of topics, including body image, mood and anxiety, and nutrition. A primary focus on CBT-E and DBT was chosen because of the research evidence supporting their use for disorders characterized by binge eating. Trauma-informed care was also part of the treatment program. The average length of stay in the BETR program is 30 days, although this can vary considerably based on patients’ progress and insurance coverage.

### Measures

#### Primary Outcomes: Eating Behavior

The Eating Pathology Symptoms Inventory (EPSI) [31] is a 45-item self-report measure of eating pathology with eight subscales: body dissatisfaction, binge eating, cognitive restraint, purging, restricting, excessive exercise, negative attitudes toward obesity, and muscle building. Items are scored on a 5-point scale from 0 (never) to 4 (very often). The EPSI has been shown to have good psychometric properties [32].

The Binge Eating Scale (BES) [33] is a 16-item self-report measure assessing binge eating behaviors that may be indicative of an eating disorder. It measures eating disordered behaviors as well as feelings associated with a binge episode. Items are measured on a 4-point scale, and the measure has been shown to have good psychometric properties [34].

The Night Eating Questionnaire (NEQ) [35] is a 14-item self-report measure of various aspects of night eating, including percentage of food consumed after dinner and frequency of nocturnal awakenings and ingestion of food. Items are scored on a 5-point scale.

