**Results:**

The primary aim is to assess the impact of the program on eating disordered behaviors at discharge and 12-month follow-up, which are hypothesized to improve as a result of treatment. Secondary hypotheses include improvements on comorbid symptoms, including trauma, depression, and obsessive-compulsive symptoms, as well as improvements on medical indicators of health, including cholesterol and triglycerides, at discharge and 12-month follow-up.

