### Primary Hypotheses

It is hypothesized that meaningful improvements (defined here as pre- to posttreatment change with at least a medium Cohen *d* effect size of 0.5) will be demonstrated on measures of eating disorder psychopathology as a result of treatment addressing binge eating and other disordered eating behaviors. It is also hypothesized that a history of trauma and current posttraumatic stress disorder (PTSD) symptoms will moderate treatment effects, in that improvements in eating disorder symptoms will be less marked among those with a history of trauma or current PTSD symptoms. Although some studies have found that PTSD does not result in poorer treatment outcomes for binge eating [19,20], other studies have found that PTSD predicts more binge eating at end of treatment [21] and premature treatment dropout for patients with BN [22]. Given these mixed findings and the assumed increased level of severity in the current population seeking higher level of care treatment, PTSD will be examined as a moderator.

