### A Priori Analytic Plan

All data at admission, discharge, and 3, 6, and 12 months postdischarge will be aggregated for the full sample and examined for patterns of missingness, outliers (>3 standard deviations from mean), and normality of distributions. Our a priori assumptions are that data will be missing at random, and all data will be normally distributed with the appropriately minimal proportion of outlier data points. Mixed models will be used to examine fixed and random effects of linear within-person change in BDI-II, EDQOL, OCI-R, STAI, RSE, DAS-SF, PCL-5, BES, and NEQ across our major timepoints of interest (admission, discharge, and 12-month follow-up). Mixed models will be run both unadjusted, as well as adjusted for person-level variables of BMI at admission, demographic variables of age, race/ethnicity, and gender, and diagnosis. Lastly, to examine the potential for different trajectories within-treatment and posttreatment, nested model comparisons will be conducted comparing the linear mixed models described above with mixed models including a quadratic time variable. Based on an expected effect size of at least *d*=0.5, and to account for a range of potentially inflated intraclass correlation coefficients that could reduce power, a sample size of 100 was determined to be sufficient to test both the mixed effects main effect hypotheses above, as well as the mixed effects 2-level interactions specified below.

All data at each of these timepoints will also be subset by patients above and below the threshold for history of trauma (defined as an ACES score ≥4) and above and below the most commonly established threshold for clinically significant levels of PTSD symptoms via the PCL-5 (PCL-5 ≥33) [48]. These subsets of patients will be compared using independent-samples *t* tests to determine any differences in point-prevalence of BDI-II, EDQOL, OCI-R, STAI, RSE, DAS-SF, BES, and NEQ by history of trauma or current trauma symptoms, and traditional moderation analyses with interaction terms added to the mixed models described above to determine any differences in changes over time of BDI-II, EDQOL, OCI-R, STAI, RSE, DAS-SF, BES, and NEQ by history of trauma or current trauma symptoms.

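### The primary success threshold of d ≥ 0.5 is attached to an unranked set of two to ten scores at one or two times, with no deciding score and no any/most/all rule

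*Protocol article*

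**What the plan says.** - **Primary instruments** (Methods, Primary Outcomes: Eating Behavior). Three are listed together without rank. The EPSI "is a 45-item self-report measure of eating pathology with eight subscales"; no total score is described for it, whereas the EDQOL entry under Secondary Outcomes does mention a total. The BES "is a 16-item self-report measure assessing binge eating behaviors that may be indicative of an eating disorder". The NEQ "is a 14-item self-report measure of various aspects of night eating".
- **Times** (Abstract, Results). "The primary aim is to assess the impact of the program on eating disordered behaviors at discharge and 12-month follow-up".
- **Success rule** (Introduction, Primary Hypotheses). Meaningful improvement is defined as "pre- to posttreatment change with at least a medium Cohen *d* effect size of 0.5", and it "will be demonstrated on measures of eating disorder psychopathology as a result of treatment addressing binge eating" and other disordered eating.
- **Analysis** (A Priori Analytic Plan). Mixed models of linear change over admission, discharge and 12 months are planned for a list of scores that contains the BES and NEQ but not the EPSI. The moderation list omits the EPSI too. The sample of 100 is justified by an "expected effect size of at least *d*=0.5".

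**The concern.** The article fixes the primary outcome as a set and attaches one threshold to it, but gives no rule for turning several estimates into one conclusion. Choosing the primary outcome belongs in the protocol, so an unseen analysis plan does not cover this.

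It matters more here than usual. There is no comparator, and the Discussion relies on prespecified hypotheses about the degree of improvement for the study's value. The d threshold is the only stated success criterion for the primary hypothesis, so the scores it applies to need to be fixed. As written, the same results could be reported as supporting the hypothesis because one score crossed 0.5, or as not supporting it because one score did not. Either reading could be chosen after the data are seen.

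**Working it through.** **Count.** EPSI 8 + BES 1 + NEQ 1 = 10 scores. Two primary times give up to 10 × 2 = 20 estimates. If pre- to posttreatment means admission to discharge only, there are 10. If the analytic plan's list defines the set (BES and NEQ), there are 4 or 2.

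**The plan's own figure.** N=100 cannot be reproduced, because no alpha, power or intraclass correlation value is given. Assuming a two-sided 5% test and 80% power, a paired contrast at d=0.5 needs ((1.96 + 0.84)/0.5)² = 31.4, so 32 patients; 100 patients give 99.9% power. The sample is therefore ample for showing *some* change. An observed d of at least 0.5 is a different event: if the true d is 0.5, one estimate reaches 0.5 half the time, whatever the N.

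**Main set-up (assumptions, not document figures).** With a pre–post correlation r of 0.5, the variance of change is 2(1 − r)σ² = σ², so SE(d) ≈ 1/√100 = 0.1. Estimates are multivariate normal, with correlation 0.2, 0.4 or 0.6 between scores and 0.5 between times (multiplied for different scores at different times). A second set-up uses SE = √(1/N + d²/(2N)) and one common correlation from 0 to 0.7.

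**Probability of success at true d = 0.5 on every score, N=100**

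| Reading of the primary set | Correlation | Any ≥ 0.5 | All ≥ 0.5 |
|---|---|---|---|
| 10 scores, 2 times | scores 0.2–0.6, times 0.5 | 96–99.8% | 0.2–4% |
| 10 scores, 2 times | common 0–0.7 | 88–100% | 0–12% |
| 10 scores, 1 time | common 0–0.7 | 83–100% | 0–17% |
| BES and NEQ, 2 times | common 0–0.7 | 73–94% | 6–27% |
| BES and NEQ, 1 time | common 0–0.7 | 63–75% | 25–37% |
| One named score, 1 time | – | 50% | 50% |

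A majority rule over 20 estimates gives 41–49%. With N=70 as a dropout case the picture at d=0.5 is the same, because the true value sits on the threshold and the SE cancels.

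**Just below the threshold, true d = 0.4 everywhere (main set-up).** One named score: P(Z > (0.5 − 0.4)/0.1) = P(Z > 1) = 16%. At least one of 20: 66–86%.

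**Larger effects (main set-up, 20 estimates).** *Any* is essentially 100%. *All* is 14–34% at d=0.6, 70–81% at 0.7 and about 98% at 0.8 (91–96% at 0.8 in the second set-up).

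**No change at all.** P(any of 20 reaches 0.5) ≤ 20 × P(Z > 5) = 20 × 2.87×10⁻⁷ ≈ 0.0006%.

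**One score required at both times, true d = 0.5, time correlation 0.5.** 1/4 + arcsin(0.5)/(2π) = 0.25 + 0.083 = 33%.

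**The case against.** The strongest reply is that this is an uncontrolled pragmatic study that promises no single go/no-go verdict, and that reporting d for each measure is a natural reading of a hypothesis about several measures. Multiplicity adjustment is also commonly left to an analysis plan. Both points are fair, and the absence of an adjustment is not the complaint. But the article states a primary hypothesis with a numerical threshold and does not say which scores test it. A per-measure report would still leave open when that hypothesis is supported.

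Three stronger readings are tempting and should not be drawn:

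- *Type I error is lost.* A reader might compute 1 − 0.95²⁰ = 64% for at least one false positive in 20 independent tests. That uses p<0.05, which is not the plan's success rule. Under the d ≥ 0.5 rule a program with no effect almost never passes (about 0.0006%). The exposure is to a near miss, such as a true d of 0.4, being called a success. If success meant significance alone, *all of 20* would pass about 98–99% of the time at d=0.5.
- *The verdict always runs from near-certain failure to near-certain success.* That holds for ten scores at two times with true effects at about the threshold. The plan expects at least 0.5, and the gap shrinks as effects grow. With the BES and NEQ alone it is wide, but neither reading is near-certain.
- *Several EPSI subscales are irrelevant to the program.* The Treatment section covers body image and compulsive exercise, and patients with bulimia nervosa are included, so purging is relevant. Muscle building is the one subscale clearly outside the stated targets.

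**Conclusion.** The point stands in this form: the primary set is unranked, has no deciding score or combining rule, and is of uncertain size because the EPSI is primary in the outcomes section but absent from the analytic plan's model lists. None of the readings of the set (ten scores or two, one time or two) removes the ambiguity at the plan's own planning effect. At true d=0.5, *any* against *all* is 96–99.8% against 0.2–4% on the widest reading and 63–75% against 25–37% on the narrowest.

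These sizes rest on N=100, assumed correlations and a common true effect. They are smaller at high correlation (88% against 12% for 20 estimates at 0.7) and nearly vanish if every score truly changes by 0.8. The absence of a deciding rule does not depend on these assumptions. This should be corrected before analysis.

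**What to change.** Before outcomes are examined:

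1. Name one deciding score. BES total is an example: it is specific to binge eating and already in the analytic plan's models.
2. Name one deciding timepoint. Alternatively, require both discharge and 12 months, accepting about a 33% chance of observing d ≥ 0.5 at both when the true d is 0.5 (time correlation 0.5).
3. Report the NEQ and the EPSI subscales as supportive.
4. Reconcile the EPSI: add it to the analytic plan's list of modelled scores, or drop its primary status.

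The cost is about a paragraph of text, and the other primary scores lose deciding status. The Results section puts the end of data collection in May 2021 and the expected start of analysis in April 2022, so the choice can no longer be fully prospective. It should be dated and documented as made before outcomes were examined.

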#### Secondary Outcomes: Comorbid Symptoms

The Acceptance and Action Questionnaire for Weight-Related Difficulties – Revised (AAQW-R) [36] is a 10-item self-report measure of experiential avoidance of weight-related feelings, thoughts, and actions with good psychometric properties. It has three subscales: food as control, weight as a barrier to living, and weight stigma [37].

The Eating Disorders Quality of Life (EDQOL) instrument [38] is a 25-item self-report measure assessing the impact of an eating disorder on one’s quality of life. It has a total score and four subscales: psychological, physical/cognitive, financial, and work/school. Items are scored on a 5-point scale from 0 (never) to 4 (always). It has been found to have good convergent and discriminant validity and good test-retest reliability [38].

The Beck Depression Inventory-II (BDI-II) [39] is a widely used 21-item self-report measure assessing the severity of depressive symptoms. Items are scored on a 4-point scale, with total scores ranging from 0-63. The measure has been found to have adequate reliability and validity [39].

The Obsessive-Compulsive Inventory – Revised (OCI-R) [40] is an 18-item self-report measure of obsessive-compulsive symptoms. It assesses six groups of symptoms, including washing, checking, ordering, obsessing, hoarding, and neutralizing. Items are scored on a 5-point scale from 0 (not at all) to 4 (extremely). It has been shown to have good internal consistency, test-retest reliability, and convergent and discriminant validity [40].

The State-Trait Anxiety Inventory (STAI) [41] is a 40-item self-report measure of state and trait anxiety, with 20 items assessing how respondents feel “at this moment,” and 20 items assessing how respondents “generally feel.” Items are scored on a 4-point scale from 1 (not at all/almost never) to 4 (very much so/almost always). Psychometric properties have been found to be adequate [41].

The Rosenberg Self-Esteem Scale (RSE) [42] is a 10-item self-report measure of self-esteem, with items scored on a 4-point scale from 1 (strongly agree) to 4 (strongly disagree). It has been found to have excellent internal consistency and test-retest reliability [42].

The Dysfunctional Attitudes Scale – Short Form (DAS-SF 1) [43] is a 9-item measure assessing dysfunctional attitudes of individuals with depression. Items are scored on a 4-point scale from “totally disagree” to “totally agree.” The measure is highly correlated with the original 40-item version of the DAS and has good internal consistency [43].

The PTSD Checklist for DSM-5 (PCL-5) [44] is a 20-item self-report measure that assesses the DSM-5 [1] symptoms of PTSD over the previous month. There are four subscales that correspond to PTSD symptom clusters B (intrusions), C (avoidance), D (negative alterations in cognitions and mood), and E (alterations in arousal and reactivity). It has demonstrated good internal consistency, test-retest reliability, and convergent and discriminant validity among veterans [45]. It has not yet been validated in an eating disorder population. The PCL-5 will be examined as an outcome, but also as a predictor variable to determine whether patients with higher PCL scores have poorer outcomes compared to those with lower PCL scores.

The Adverse Childhood Experiences Survey (ACES) [46] is a 10-item self-report measure that assesses 10 types of childhood trauma, including physical, verbal, or sexual abuse, physical or emotional neglect, having a parent who struggles with alcoholism, having a mother who is a victim of domestic violence, having a family member in jail, having a family member diagnosed with a mental illness, and having a family member unavailable due to divorce, death, or abandonment. Adverse childhood experiences (ACEs) have been found to be related to a number of psychiatric and medical illnesses in adulthood, often with a dose-response relationship wherein risk for illness in adulthood is related to a greater number of ACEs in childhood [46]. The ACES will be examined primarily as a predictor variable to determine whether patients with more ACEs have poorer outcomes compared to those with fewer or no ACEs.

### Secondary Outcomes: Medical/Physiological Variables

At 3 and 6 months postdischarge, patients obtained a blood draw for a lipid panel (total cholesterol, HDL, LDL, triglycerides) and HbA_1c_. Patients were weighed weekly or twice weekly depending on insurance requirements and symptom presentation (ie, active purging was monitored more frequently with weights and labs). All weight collection was blind. “Blind weighing” involves not sharing weight data with the patient to minimize potential distress that may occur from the patient seeing his or her weight [47]. Table 1 displays a timeline of measures and labs that were collected.

**Table 1 table1:** Timeline of collection for labs and questionnaires.

		Baseline	Discharge	3-month follow-up	6-month follow-up	12-month follow-up
**Labs**						
	Total cholesterol	x		x	x	
	High density lipoprotein	x		x	x	
	Low density lipoprotein	x		x	x	
	Triglycerides	x		x	x	
	Glycated hemoglobin	x		x	x	
**Assessments**						
	Eating Pathology Symptoms Inventory	x	x		x	x
	State-Trait Anxiety Inventory	x	x		x	x
	Acceptance and Action Questionnaire for Weight-Related Difficulties – Revised	x	x		x	x
	Beck Depression Inventory-II	x	x		x	x
	Binge Eating Scale	x	x		x	x
	Dysfunctional Attitudes Scale – Short Form	x	x		x	x
	Eating Disorders Quality of Life	x	x		x	x
	Night Eating Questionnaire	x	x		x	x
	Obsessive-Compulsive Inventory – Revised	x	x		x	x
	PTSD Checklist for DSM-5	x	x		x	x
	Rosenberg Self-Esteem Scale	x	x		x	x

### A Priori Analytic Plan

All data at admission, discharge, and 3, 6, and 12 months postdischarge will be aggregated for the full sample and examined for patterns of missingness, outliers (>3 standard deviations from mean), and normality of distributions. Our a priori assumptions are that data will be missing at random, and all data will be normally distributed with the appropriately minimal proportion of outlier data points. Mixed models will be used to examine fixed and random effects of linear within-person change in BDI-II, EDQOL, OCI-R, STAI, RSE, DAS-SF, PCL-5, BES, and NEQ across our major timepoints of interest (admission, discharge, and 12-month follow-up). Mixed models will be run both unadjusted, as well as adjusted for person-level variables of BMI at admission, demographic variables of age, race/ethnicity, and gender, and diagnosis. Lastly, to examine the potential for different trajectories within-treatment and posttreatment, nested model comparisons will be conducted comparing the linear mixed models described above with mixed models including a quadratic time variable. Based on an expected effect size of at least *d*=0.5, and to account for a range of potentially inflated intraclass correlation coefficients that could reduce power, a sample size of 100 was determined to be sufficient to test both the mixed effects main effect hypotheses above, as well as the mixed effects 2-level interactions specified below.

All data at each of these timepoints will also be subset by patients above and below the threshold for history of trauma (defined as an ACES score ≥4) and above and below the most commonly established threshold for clinically significant levels of PTSD symptoms via the PCL-5 (PCL-5 ≥33) [48]. These subsets of patients will be compared using independent-samples *t* tests to determine any differences in point-prevalence of BDI-II, EDQOL, OCI-R, STAI, RSE, DAS-SF, BES, and NEQ by history of trauma or current trauma symptoms, and traditional moderation analyses with interaction terms added to the mixed models described above to determine any differences in changes over time of BDI-II, EDQOL, OCI-R, STAI, RSE, DAS-SF, BES, and NEQ by history of trauma or current trauma symptoms.

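### The main mixed models assume missing at random without admission PCL-5 or ACES, so the overall 12-month improvement may be overstated if PTSD or trauma drives both loss to follow-up and response

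*Protocol article*

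**What the plan says.** All places are in the protocol article.

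- **A Priori Analytic Plan, missing data.** The data will be "examined for patterns of missingness", and the assumption is fixed in advance: "Our a priori assumptions are that data will be missing at random". No action is tied to what the examination shows.
- **Same section, main models.** Linear change is modelled over admission, discharge and 12 months for nine scales, BES and NEQ among them. Each model is run unadjusted and then "adjusted for person-level variables of BMI at admission, demographic variables of age, race/ethnicity, and gender, and diagnosis". PCL-5 and ACES are not on that list.
- **Same section, trauma and PTSD.** Groups formed by ACES ≥4 and PCL-5 ≥33 are compared by t tests and by "traditional moderation analyses with interaction terms added to the mixed models described above".
- **Primary Hypotheses.** The authors expect that "improvements in eating disorder symptoms will be less marked among those with a history of trauma or current PTSD symptoms". On the literature they write that "other studies have found that PTSD predicts more binge eating at end of treatment [21] and premature treatment dropout for patients with BN", but the same sentence opens by conceding that "some studies have found that PTSD does not result in poorer treatment outcomes for binge eating [19,20". They call the findings mixed.

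**The concern.** A likelihood-based mixed model is valid under missing at random only given what the model contains: the observed scores of the outcome and the listed covariates. If a variable outside the model affects both the chance of a 12-month score and the size of the change, patients who stay differ from those who leave in a way the model cannot fully see. The protocol names a candidate, hypothesises its effect on response, cites some evidence of a link to treatment dropout, and then leaves it out of the models that estimate overall change.

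The study has no control group, and the Discussion rests its value on the degree of improvement. The criterion for a meaningful improvement is d of at least 0.5, so a modest upward shift can turn a result just short of the criterion into one that meets it.

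The Discussion also says that evaluating consecutive admissions without a research overlay limits biased missing data. That holds at most for admission and discharge, where questionnaires are routine though optional. According to Study Procedures, the 12-month questionnaires are part of the extra data collection for this study.

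**Working it through.** **Inputs.** From the protocol: 100 patients, three main timepoints, threshold d = 0.5, and the covariate list above. It gives no retention rate, PTSD prevalence, subgroup effect or within-person correlation, so there is no plan figure to reproduce. Everything below is assumed: PTSD share p of 30-50%; 12-month change d0 without and d1 with PTSD; 12-month retention r0 without and r1 with PTSD.

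**Step 1: size by hand, patients with 12-month data only.** The PTSD share among those retained is q = p·r1 / [p·r1 + (1−p)·r0]. The true average change is d0 − p(d0−d1). Those retained show d0 − q(d0−d1). The bias is therefore (p−q)(d0−d1).

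- Retention 70%/70%: q = p, bias 0.
- p = 0.5, 80%/60%: q = 0.30/0.70 = 0.429. Bias 0.071 × 0.4 = 0.029 for 0.7 vs 0.3, and 0.071 × 0.6 = 0.043 for 0.8 vs 0.2.
- p = 0.5, 80%/40%: q = 0.20/0.60 = 0.333. Bias 0.167 × 0.4 = 0.067, and 0.167 × 0.6 = 0.100.
- p = 0.3, 80%/40%: q = 0.12/0.68 = 0.176. Bias 0.124 × 0.4 = 0.049, and 0.124 × 0.6 = 0.074.

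**Step 2: the mixed model.** The model also uses the admission and discharge scores of patients lost later. These can recover part of the bias when discharge is well observed, or add to it when PTSD patients start worse. A simulation covered both: 60,000 patients per scenario, within-person correlation 0.5, PTSD patients level with the others or 0.5 SD worse at admission, discharge complete or also subject to loss, p of 30% or 50%. Bias in the 12-month change with PTSD ignored:

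| Retention (without/with PTSD) | Change (without/with PTSD) | True average | Bias, SD |
|---|---|---|---|
| 70%/70% | 0.7 / 0.3 or 0.8 / 0.2 | 0.50-0.62 | about 0 |
| 80%/60% | 0.7 / 0.3 | 0.50-0.58 | 0.01-0.03 |
| 80%/60% | 0.8 / 0.2 | 0.50-0.62 | 0.02-0.04 |
| 80%/40% | 0.7 / 0.3 | 0.50-0.58 | 0.03-0.08 |
| 80%/40% | 0.8 / 0.2 | 0.50-0.62 | 0.05-0.10 |
| 80%/40% | 0.6 / 0.6 | 0.60 | about 0; up to 0.03 if PTSD patients start worse |

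Fitting within PTSD groups and averaging over the PTSD share of the full sample returned the true value to within simulation error, about 0.01.

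**Step 3: the threshold.** Adding one constant to both groups' changes moves the truth and the estimate alike and leaves the bias unchanged. With p = 0.5, 80%/40% and a difference of 0.4 between groups, the simulated bias is 0.04-0.08. A true value from 0.50 − 0.04 = 0.46 (or 0.50 − 0.08 = 0.42) up to just under 0.50 would then be reported as 0.5 or more. At 80%/60%, with a bias of at most 0.03, that band begins at 0.47.

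**Step 4: which term is needed.** A PTSD main effect shifts all visits equally. It can absorb a difference in level but not a difference in change, and the latter produces (p−q)(d0−d1). The by-visit interaction, averaged over the full sample, is required.

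**Limit.** The simulation used categorical time and an unstructured covariance. With time coded by visit, a quadratic through three visits fits three means freely, so this is close to the plan's quadratic model. The linear model was not simulated, nor was any bias at discharge quantified.

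**The case against.** The strongest objection concerns the evidence. A reader might infer that the protocol itself states that PTSD and trauma predict both dropout and poorer response, and hence that the 12-month result is overstated. It does not say this. Poorer response is a hypothesis, set against findings the authors call mixed. The dropout evidence is for PTSD only, in BN only (the program also treats BED), and for leaving treatment. Trauma history is not linked to dropout at all. A patient who leaves treatment early can still return a 12-month questionnaire, for which a gift card is offered. All of this stands, and it is why the point is conditional.

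Second, the plan already fits interactions of trauma and PTSD with time, for BES and NEQ among others, and moderation is itself listed under Primary Hypotheses. This stands in part: the terms exist, but dichotomised and to test moderation. Nothing says that they supply the overall change.

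Third, the bias is small beside sampling error. With 60 patients observed and an assumed SD of change of 1, the standard error is 1/√60 = 0.13, larger than any bias in the table. That is true, but the bias does not average out and always favours the hypothesis in the settings where it arises.

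Fourth, auxiliary variables and sensitivity analyses are often left to a fuller plan. This holds for the sensitivity analysis, which is therefore only a supplement here. It does not cover the covariate list, which the article states.

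**Conclusion.** The concern holds in conditional form. The plan assumes missing at random in models that leave out two measures it expects to affect response, one of which it links, on limited evidence, to treatment dropout. If PTSD or trauma drives both loss to follow-up and response in this sample, the overall 12-month improvement is overstated. The size is about 0 at equal retention, 0.01-0.04 SD at 80%/60%, and up to about 0.10 SD at 80%/40%. These figures rest wholly on assumed prevalence, retention, effects and correlation, and the upper end also depends on how discharge data are lost.

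Two stronger readings are not supported. The documents do not show that the improvement **is** overstated, since without differential loss the bias vanishes. Nor do they show that the 0.5 threshold would be wrongly crossed; this happens only if the true value lies in a narrow band below it. A fall from 0.70 to (1 − 0.30) × 0.70 = 0.49, with 30% missing and all of them back at admission level, is a different scenario. It does not depend on PTSD, and adding PCL-5 would not cure it.

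The change is worth making because it is cheap, not because an error is proven.

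**What to change.** - For the overall change in BES and NEQ, add admission PCL-5 (continuous) and ACES score, each by visit, and report the change averaged over the admission distribution of all enrolled patients. Alternatively, use both as auxiliary variables in multiple imputation. A main effect alone is not enough.
- Do the same for EPSI once a model for it is specified. It is a primary outcome under Measures but is not among the mixed-model outcomes.
- State that this model, and not the moderation test, supplies the overall 12-month estimate.
- As a supplement, report the 12-month delta at which d falls below 0.5. If a fraction m is missing and the missing-at-random estimate is d, the tipping shift is (d − 0.5)/m. For example, (0.70 − 0.50)/0.30 = 0.67 SD.

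The cost is a few more parameters at N=100 and one extra run. No new data should be needed: PCL-5 is collected at baseline, and ACES is already a planned predictor. Table 1 does not show when ACES is collected, so its availability for patients lost early should be confirmed.
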